### Timeline

A general study timeline is depicted in Fig. 4. Significant preparation prior to trial commencement was required and included completion of the IRB processes at multiple institutions, baseline hospital assessment, selection, and allocation, and staff training and site preparation. This phase was expected to take approximately 14 months. Once the study began, implementation and enrollment were anticipated to take 9 months, and follow-up a further 12 months. After trial completion, data analysis and reporting was planned for the following 12 months.

**Fig. 4 Fig4:**
[figure not shown]
Timeline of the Study. The study was expected to require approximately 14 months for pre-implementation preparation (i.e. IRB preparation, submission, review, and approval; baseline hospital assessment, selection, and allocation; and staff training and site preparation). Implementation and enrollment were expected to take a further 9 months, and follow-up required a subsequent 12-month period. Finally, data analysis and reporting were expected to require another 12 months. (institutional review board [IRB], antiretroviral therapy [ART])

### Data collection, management, and monitoring

Baseline assessment information, including participant contact and demographic information, laboratory screening results and dates, test result notification dates, and post-test counseling dates were all collected using case reporting forms (CRFs). CRF data were stored in a web-based database constructed specifically for the study. This database served as the centralized location for electronic storage of all study-related data. Study-related data from each hospital system was retrieved weekly and uploaded to this study database.

To supplement the data contained in the study-specific database, records were extracted from CRIMS [20]. Each county hospital nationwide, including all participating study hospitals, have unique identification codes in CRIMS to facilitate extraction of all data on HIV cases identified at study hospitals.

A centralized Data and Statistics Team (DST) was responsible for the validation of the web-based study database, retrieval of study hospital data, data extraction from CRIMS, merger of the two datasets into one, assurance of data integrity and security, and development and delivery of training for participating hospital and CDC staff members on applicable data management procedures.

### Data analysis

To adjust for both the clustering effect of hospitals (with hospital as a random effect to account for the ICC) and baseline participant-level and hospital-level confounding factors, analysis of the primary outcome measure was performed using G-side GLIMMIX modeling. Participant-level factors included in the model were age, gender, ethnicity, education, occupation, marital status, transmission route, and treatment setting (inpatient/outpatient), and hospital-level factors included baseline test completion rate prior to randomization. To assess the consistency of the primary outcome results, a Chi-square test adjusted for clustering was also used to measure the association between treatment arm and the primary outcome [21], although this method does not account for baseline confounders. Secondary analyses of the primary outcome measure were performed as a waiting time analysis examining time from initial positive screen to success. For this waiting time analysis, participants who did not meet the testing success criteria were censored at their last follow-up dates. Kaplan-Meier curves were used to display differences over time from screening to testing and counseling completeness.

In comparing differences in baseline characteristics between the two arms, a Chi-square test adjusted for clustering was performed for binary variables. When baseline categorical variables had more than 2 responses, an adjusted *p*-value was calculated by referring the observed (unadjusted) Chi-square value to the distribution of Chi-square values obtained by randomly permuting observed treatments over hospitals, with the adjusted *p*-value defined as the proportion of 'permuted' Chi-square values at least as large as observed. To test between-arm differences in continuous data, a *t*-test adjusted for clustering was performed [21].

Analytical methods and the adjustment for clustering and covariates effects used in the analysis of the primary outcome were also applied to the ART initiation secondary outcome and viral suppression tertiary outcome. As with the secondary analysis of the primary outcome, Kaplan-Meier analyses were also performed for time to initiation of ART, outside the 90-day window, and time to death. In addition, for the mortality outcome, a random effects Cox (shared frailty) model accounting for the hospital clustering effect was used to calculate the intervention effect on the hazard ratio (HR) of death while also controlling for other covariates. Adjustments to *p*-values and confidence intervals for multiple testing and multiple comparisons were not performed. All data analyses were performed using SAS software (SAS Institute, Inc., USA).

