## Method

### Design

A cluster-randomized trial was designed as diagrammed in Fig. 1. Hospitals were the unit of randomization and twelve similar county-level hospitals were allocated one-to-one to the intervention and control arms of the study. The efficacy of the intervention was determined by comparison to the current standard of care (SOC, control arm) at 30 days, 90 days, and 12 months.

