### Allocation and blinding

The twelve selected study hospitals were stratified by historical rates of testing completeness followed by post-test counseling during the first six months of 2013 prior to being allocated to the intervention or control study arms. Eight hospitals were within the low historical testing completion stratum of <20%, and these eight hospitals were randomized, four into the intervention arm and four into the control arm. Four hospitals were within the high historical testing completion stratum of ≥20%, and these four hospitals were randomized, two into the intervention arm and two into the control arm. All patients who screened HIV-positive in the six intervention hospitals received the One4All intervention and all patients who screened HIV-positive in the six control hospitals during the same study period received SOC services. There was no blinding required since the unit of randomization was the study hospital and each hospital only offered the HIV care cascade it was assigned during randomization—SOC or One4All.

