### Sample size

A minimum sample size of 180 participants per arm, across 12 clusters (or 30 participants per cluster) was selected. This sample size was expected to achieve 93% power based on a one-sided test (at alpha = 0.05) to detect a difference between the group proportions of 0.28, where under the alternative hypothesis the One4All arm proportion was assumed to be 0.50 and the control arm proportion was assumed to be 0.22. This calculation assumed an intra-class correlation (ICC) within hospitals of 0.082 based on preliminary data. Although 30 participants per cluster (or hospital) was the target, it was expected that some hospitals would enroll participants more quickly than others. Therefore, a final study population of greater than 180 participants per arm was anticipated as enrollment at all hospitals remained open until the last hospital met its 30-participant goal.

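### The cluster-adjusted chi-square check allows for neither the 12 hospitals nor the stratified allocation, so it does not hold its 5% level; the GLIMMIX test shares the small-sample fault only if it lacks between-hospital degrees of freedom

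*Protocol article*

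**What the plan says.** Design: "Hospitals were the unit of randomization and twelve similar county-level hospitals were allocated one-to-one to the intervention and control arms of the study". Allocation and blinding: the hospitals were first stratified by historical testing completeness. "Eight hospitals were within the low historical testing completion stratum of <20"%, and these were split 4:4. The other four were split 2:2.

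Data analysis, primary outcome: "analysis of the primary outcome measure was performed using G-side GLIMMIX modeling", with hospital as a random effect, eight participant-level covariates and the hospital's baseline completion rate. The section gives no denominator degrees of freedom, reference distribution or sidedness. As a check on consistency, "a Chi-square test adjusted for clustering was also used to measure the association between treatment arm and the primary outcome". The article concedes that this check ignores baseline confounders. It then applies the primary-outcome methods to ART initiation and viral suppression, without multiplicity adjustment.

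A permutation test is described only for baseline categorical variables with more than two levels. It works by "randomly permuting observed treatments over hospitals", and no restriction to the two strata is mentioned.

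The only alpha stated is in Sample size: "This sample size was expected to achieve 93% power based on a one-sided test (at alpha = 0.05").

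**The concern.** The arm effect is a contrast between six hospitals and six hospitals. However many patients are enrolled, its error variance is estimated from about 10 degrees of freedom, or 9 once the baseline rate is in the model. A 1-df chi-square reference treats that variance as known, which makes the test too liberal.

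A second fault acts in the other direction. Allocation was balanced on historical completion. If history predicts the outcome, an unstratified test counts the between-stratum spread as error, although the design removed it from the arm contrast, and the test becomes conservative.

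The check can therefore err either way, and the reader cannot tell which. Agreement or disagreement with the primary model at 5% then says little. This matters for three outcomes, because the same methods are reused and each p-value is read at its nominal level.

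**Working it through.** **1. The plan's own figure.** Inputs from Sample size: 180 per arm, 30 per hospital, ICC 0.082, 0.50 versus 0.22, one-sided alpha 0.05.

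- Design effect = 1 + 29 × 0.082 = 3.378.
- Effective n per arm = 180 / 3.378 = 53.3.
- Unpooled SE = √[(0.50 × 0.50 + 0.22 × 0.78) / 53.3] = √(0.4216 / 53.3) = 0.0889.
- Power = Φ(0.28 / 0.0889 − 1.645) = 93.4% (92.3% with a pooled SE).

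The stated 93% reproduces with normal critical values. With t critical values on 9-10 df it is about 90% one-sided and 80-81% two-sided. So the design figure makes no allowance for having 12 clusters. This does not show which df the analysis used.

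**2. Analytic size of a large-sample test.** Degrees of freedom: 12 − 2 = 10, or 12 − 3 = 9 with the baseline rate.

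| True reference | Two-sided, P(abs t > 1.960) | One-sided, P(t > 1.645) |
|---|---|---|
| t, 10 df | 7.8% | 6.6% |
| t, 9 df | 8.2% | 6.7% |

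Residual (patient-level) df give nearly the same result: 7.8% and 8.1% two-sided.

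**3. Simulated size, nominal two-sided 5%.** Beta-binomial outcomes in 12 hospitals, allocated 4:4 and 2:2 within strata, 3,000-4,000 null trials per scenario. The ICC of 0.082 is from the article. The other ICCs (0.04, 0.15, and 0.05 within strata), the unequal hospital sizes and the stratum rates are assumptions. The adjusted chi-square is taken in its usual form: an ANOVA estimate of the ICC and a 1-df reference.

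| Test | Strata do not predict outcome | Rates 0.18 vs 0.30 | Rates 0.14 vs 0.38 |
|---|---|---|---|
| Adjusted chi-square | 7.1-8.4% | 4.4-4.8% | 1.2-1.4% |
| Random-intercept logistic with stratum, normal reference | 7.7-8.6% | 7.2% | 7.2% |
| Same model, t on 9 df | 4.4-5.4% | 4.4% | 4.2% |

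Where strata do not predict outcome, the one-sided size at nominal 5% of the random-intercept model with a normal reference, with or without stratum, is 6.3-7.2%.

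**4. Permutation within strata.** The design allows C(8,4) × C(4,2) = 70 × 6 = 420 allocations. Permuting freely over 12 hospitals gives C(12,6) = 924, of which 924 − 420 = 504 (55%) could not have occurred.

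- On hospital-level proportions, the 420-allocation test has a size of about 3.5% in these scenarios. A repeat run gave 3.3-4.7%, with the lower values at exactly 30 per hospital, where tied differences are common.
- It stays below 5% whether or not the strata predict outcome. Its smallest two-sided p-value is 2/420 = 0.005.

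**5. The baseline permutation.** For a three-level baseline variable, the unrestricted test has size 4.9% if the strata are unrelated to the variable and 3.4% if they are related. Restricted to the strata, it has 4.9-5.0%.

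**The case against.** The strongest objection concerns the primary analysis. A reader might infer from the article that the GLIMMIX test rejects a true null about 8% of the time. The text does not support that. It names the model and is silent on denominator df, which an article may leave to the full protocol or SAP. With 9 df the same model has a size close to 5%. This objection stands, and the GLIMMIX part is conditional for that reason.

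The figure of 8% is also two-sided, whereas the only alpha in the article is one-sided 0.05. On that scale the inflation is smaller, to between 6% and 7%. This stands too.

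For the chi-square, one can say that stratifying presumes history predicts outcome, so the test may well be conservative. One can add that it is only a secondary check, and that its exact form lies in a cited source not available here. This removes any claim that the check is simply too liberal. It does not rescue the check, because a test whose real level may be 1% or 8% cannot corroborate a result at 5%.

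Finally, a reader might count the unrestricted permutation as a further source of false positives. It is not: it touches only multi-level baseline variables and errs on the conservative side.

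The simulations omit the eight participant-level covariates, and the article gives no ICC for ART initiation or suppression. The sizes are therefore indicative for the planned model and for those two outcomes.

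**Conclusion.** The point holds for the chi-square check, which is a stated method that does not fit the stated design. Its size at a nominal two-sided 5% is about 7-8% if the strata do not predict outcome and about 1-5% if they do. The first range rests on 12 hospitals and on ICCs around the article's 0.082. The second rests on assumed stratum rates and a within-stratum ICC of 0.05.

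For the GLIMMIX arm test the point is conditional. The size is about 8% two-sided, or 6.3-7.2% one-sided, only with normal or residual-df critical values, and close to 5% with between-hospital df. The article does not say which was used, so a claim that the primary analysis is inflated is not established.

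The baseline permutation is a minor mismatch with the allocation and carries no false-positive risk for any outcome.

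**What to change.** 1. Replace the adjusted chi-square as the consistency check, for the primary outcome and for ART initiation and viral suppression. Use a permutation test on hospital-level proportions over the 420 within-stratum allocations.
2. State that the GLIMMIX arm effect is tested, and its interval formed, with between-hospital df: about 9 with the baseline rate in the model. State whether the test is one- or two-sided. If the full protocol or SAP already fixes this, a sentence in the article is enough.
3. As a minor point, restrict the baseline permutation to the two strata.

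The cost is a model option and a short program; the article already describes permuting hospitals, so little of it is new. Two-sided 95% intervals on 9 df are about 15% wider than normal ones (2.262 / 1.960 = 1.154). Nominal power falls from 93% to about 90% one-sided, or about 80% two-sided.

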## Background

In both resource-rich and resource-limited settings alike, patients are commonly lost at each step along the care cascade of infection with human immunodeficiency virus (HIV) that causes acquired immunodeficiency syndromes (AIDS) [1]. In China, the current standard-of-care (SOC) patient pathway from screening HIV-positive to initiating antiretroviral therapy (ART) involves multiple hospital visits, during which patients submit to several separate blood draws, and then experience protracted waiting periods before they are notified of results. This causes substantial loss to follow-up, delays in diagnosis, clinical assessments that are incomplete, and ART initiation at later stages of disease progression [2, 3]. Recent studies have indicated that, in some parts of China, only approximately 43% of those who screen HIV-positive in hospital settings received confirmatory testing [3], and only 57% of those confirmed HIV-positive received CD4 testing within 6 months [4]. Since CD4 count has been used to determine eligibility for ART, it has been estimated that nearly 80% of those with newly-identified HIV infection, who were ART-eligible, were not initiated on ART in a timely fashion. Unfortunately, these missed opportunities for engagement in the HIV care cascade has ultimately translated to preventable high mortality [2, 5].

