### Outcomes

The primary outcome measure was the proportion of participants who achieved testing completeness and received test results and post-test counseling within 30 days of positive screening. Testing completeness was defined as completion of three required components: 1) initial HIV screening (one to two tests in One4All and two to four in SOC), 2) CD4 testing, and 3) confirmatory HIV testing—WB in the SOC arm, or VL in the One4All arm. “Success” was defined as completion of all three required tests and notification of test result along with receipt of counseling after each test. Success was compared at 30 days after initial HIV-positive screening. The secondary outcome measure was the proportion of participants who initiated ART within 90 days from the date of HIV-positive screening. ART-initiation was defined as the receipt of the first ART prescription. Tertiary outcomes included the proportion of participants who achieved viral suppression (≤200 copies/mm^3^) and mortality at 12 months. Mortality was assessed as the number of reported deaths divided by the number of patients enrolled.

Aside from these main outcome measures, three other measures were pre-specified. For the primary outcome, two further analyses were planned: time from initial positive HIV screen to success, not restricted to the 30-day window, compared between control and intervention arms, and success at 45, 60, and 90 days, also compared between control and intervention arms. For the secondary outcome, one further analysis was planned: time from initial positive HIV screen to ART initiation, not restricted to the 90-day window, compared between control and intervention arms.

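### The waiting-time curves censor drop-outs and deaths as if they could still complete, which overstates completion in both arms if last follow-up means last contact

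*Protocol article*

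**What the plan says.** The Outcomes section of the Protocol article pre-specifies a further analysis of the primary outcome: "time from initial positive HIV screen to success, not restricted to the 30-day window, compared between control and intervention arms". The Data analysis section gives the method. "Secondary analyses of the primary outcome measure were performed as a waiting time analysis examining time from initial positive screen to success", and in it "participants who did not meet the testing success criteria were censored at their last follow-up dates". The display is by Kaplan-Meier: "Kaplan-Meier curves were used to display differences over time from screening to testing and counseling completeness".

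For the other outcomes, and by analogy with that analysis, "Kaplan-Meier analyses were also performed for time to initiation of ART, outside the 90-day window, and time to death". No separate censoring rule is given for time to ART, so the rule quoted above is the one implied. No handling of death before the event is stated for time to success or time to ART.

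The primary outcome itself is binary: "the proportion of participants who achieved testing completeness and received test results and post-test counseling within 30 days of positive screening". Success at 45, 60 and 90 days and ART initiation within 90 days are also proportions.

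**The concern.** Kaplan-Meier is valid when a person censored on day t has the same later chance of the event as those still under observation on day t. The article's own rationale says otherwise. Of the several visits and long waits in the SOC pathway, the Background says: "This causes substantial loss to follow-up, delays in diagnosis, clinical assessments that are incomplete". A patient who walks away after screening and does not return has failed in exactly the way the trial is meant to measure. Under the written rule, read as individual dates, that patient leaves the risk set on the last day seen, and the curve is computed as if he or she would have completed like those who stayed.

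Death raises the same issue. Inpatients are eligible, and mortality is an outcome. A patient who dies before success or before a first ART prescription can never have that event, so censoring at death also pushes 1 minus Kaplan-Meier upwards.

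At stake is agreement between two pre-specified views of one endpoint. The binary analysis counts a lost patient as a failure, and the curve does not. The two could differ materially because of the censoring rule alone.

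**Working it through.** **Inputs.** Planned 30-day success is 0.22 (SOC) and 0.50 (One4All), from Sample size. In SOC, confirmation takes about 10 to 15 days, followed by a CD4 draw that takes another 10 to 15 (HIV Confirmation; CD4 Count). SOC completion before about day 20 is therefore unlikely. In One4All, CD4 is available within 30 minutes and viral load in 10 to 15 days. The article gives no rate or timing of loss for the trial, so every loss figure below is an assumption.

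**The plan's own figure.** The article states no figure for the waiting-time analysis. Its 93% power for the primary outcome is reproduced: design effect 1 + 29 × 0.082 = 3.378; effective size 180/3.378 = 53.3 per arm; one-sided power 92.3% (pooled) or 93.4% (unpooled). The censoring rule does not enter that calculation.

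**Formula.** Let p be the true 30-day success proportion and L the share of the whole arm censored before anyone completes. Only 1 − L remain at risk when completions begin, so

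1 − KM(30) = p / (1 − L).

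- SOC, L = 0.30: 0.22/0.70 = 31%.
- SOC, L = 0.50: 0.22/0.50 = 44%.
- With no early loss (L = 0), the values are the planned 22% and 50%, gap 28 points.

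**Effect on the gap.** Let f be the share of non-completers censored early, so L = f(1 − p). The last column is a simulation of 200,000 patients per arm. SOC completions fall evenly on days 20 to 30 and One4All completions on days 10 to 25; early loss is spread evenly over days 0 to 30; the remaining non-completers are followed to day 365.

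| f in SOC / One4All | SOC, day 30 | One4All, day 30 | Gap, loss before any completion | Gap, loss spread over days 0–30 |
|---|---|---|---|---|
| 0 / 0 | 22% | 50% | 28.0 | 28.0 |
| 0.25 / 0.25 | 27% | 57% | 29.8 | 28.1 |
| 0.50 / 0.50 | 36% | 67% | 30.6 | 26.7 |
| 0.73 / 0.73 | 51% | 79% | 27.6 | 22.6 |
| 0.73 / 0.25 | 51% | 57% | 6.1 | 10.5 |
| 0.73 / 0 | 51% | 50% | −1.1 | 6.0 |

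The two middle columns are for loss before any completion. With loss spread over 30 days, SOC reads 26%, 33% and 44% for f = 0.25, 0.50 and 0.73.

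The value f = 0.73 is an upper illustration. The Background cites earlier work in some parts of China in which "only approximately 43% of those who screen HIV-positive in hospital settings received confirmatory testing". If the other 57% were all last seen at screening, f = 0.57/0.78 = 0.73 and SOC would read 0.22/0.43 = 51%.

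**What equal loss means.** The gap is roughly preserved when the same share of non-completers is lost in each arm. If instead the same share of all enrolled patients were lost before any completion, the gap would widen to 0.28/(1 − L). At L = 0.30 that is 71.4% − 31.4% = 40 points.

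**The case against.** The strongest reply is that last follow-up date is not defined. Outcomes come from hospital data retrieved weekly and merged with the national HIV information system (Data collection, management, and monitoring), and deaths are counted over everyone enrolled. If last follow-up meant the end of record capture for all, walk-aways would already stay at risk and drop-out would cause no inflation. This stands as a limit on the point. But the wording assigns each participant his or her own date, nothing in the article points to a common one, and deaths would still be censored under either reading.

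Second, the size rests on assumed loss. That is right. A reader might infer from the 43% figure that 57% of SOC patients in this trial would vanish at screening. The article does not support that: the figure comes from earlier studies, and lacking a confirmatory test is not the same as being last seen on day 0.

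Third, the curves are a secondary display, and the binary results at 30, 45, 60 and 90 days already count lost patients as failures. This also stands, and it limits the consequence.

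Fourth, any bias would run against the intervention. That holds only if SOC loses a larger share of its non-completers, or loses them earlier. The calculations show that other patterns leave the gap alone or widen it.

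**Conclusion.** The point holds as a bias in the secondary analysis of time to success. It extends to time to ART by implication only. Read as individual last contacts, the rule treats drop-out and death before the event as uninformative, and 1 minus Kaplan-Meier then overstates completion in both arms. With assumed loss before any completion of 30% to 50% in SOC, day-30 completion reads 31% to 44% instead of 22%.

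Two stronger readings are tempting and not supported. One is that the curves will hide the treatment effect. A near-zero gap needs extreme contrasts, such as 60% of SOC patients against 10% of One4All patients all lost before anyone completes (0.22/0.40 = 55% against 0.50/0.90 = 56%), and the article documents no such rates. The other is that the trial's main result is compromised. The 30-day primary outcome, ART within 90 days and success at 45, 60 and 90 days are binary proportions and do not use this rule. Nor does the objection apply to time to death, where death is the event. The effect of competing deaths has not been quantified; the article gives no figure from which to do so.

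**What to change.** For time to success and time to ART initiation:

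- Define last follow-up date.
- Keep every participant without the event and not known dead at risk to a common administrative date, for example 12 months after screening, which the planned follow-up allows.
- Treat death before the event as a competing event.
- Plot cumulative incidence (Aalen-Johansen) instead of 1 minus Kaplan-Meier. With no censoring before the common date, its value on day t is the number with the event by day t divided by the number enrolled, so the curves agree with the binary proportions.
- State the rule for time to ART explicitly. Leave the time-to-death analysis as it is.

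The cost is wording and programming; no new data are needed, because completion and ART dates come from hospital records and the national system. The downside is that events outside the study data, or among participants who refuse to share data but still count as enrolled (Ethics), are treated as non-events. Censoring at last contact should therefore be shown as a sensitivity analysis, with the number and timing of losses by arm.

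### Time to testing success and time to ART are pre-specified between-arm comparisons, but the only method named for them, Kaplan-Meier, does not account for the randomised hospitals

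*Protocol article*

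**What the plan says.** All references are to the Method part of the protocol article.

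- **Design.** Hospitals, not patients, were randomised: "Hospitals were the unit of randomization and twelve similar county-level hospitals were allocated one-to-one".
- **Sample size.** Clustering is built in: "This calculation assumed an intra-class correlation (ICC) within hospitals of 0.082 based on preliminary data".
- **Outcomes.** Besides the main outcomes, the article pre-specifies "time from initial positive HIV screen to success, not restricted to the 30-day window, compared between control and intervention arms" and, for treatment, "time from initial positive HIV screen to ART initiation, not restricted to the 90-day window, compared between control and intervention arms".
- **Data analysis, time to success.** There is a waiting-time analysis with a censoring rule, and then: "Kaplan-Meier curves were used to display differences over time from screening to testing and counseling completeness".
- **Data analysis, time to ART and to death.** "Kaplan-Meier analyses were also performed for time to initiation of ART, outside the 90-day window, and time to death". The clustered model that follows is for death only: "In addition, for the mortality outcome, a random effects Cox (shared frailty) model accounting for the hospital clustering effect was used".
- **Data analysis, everything else.** Testing completeness, ART initiation and viral suppression each get a hospital random effect and a cluster-adjusted chi-square test. Baseline comparisons are also adjusted for clustering, or permuted over hospitals.

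**The concern.** Two analyses are promised as comparisons of the arms, and neither has a stated method that respects hospital randomisation. Clustering does not spoil the Kaplan-Meier curve as a description of the enrolled patients. It does invalidate the usual variance attached to the curve, and the log-rank test that commonly goes with it, because both treat patients in one hospital as independent.

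The gap shows inside the article. Time to ART and time to death share one Kaplan-Meier sentence, and only death is then given a model that handles hospitals. The sentence carrying the primary outcome's methods over to ART initiation does not clearly fill it: Outcomes defines that secondary outcome as a proportion within 90 days, and the binary-outcome model and chi-square test are not methods for censored times.

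At stake is how a reader takes a reported difference in speed through the care cascade. The article's Discussion and Conclusion speak of accelerating diagnosis and ART initiation, and the Discussion acknowledges high variability in standard care between counties. An unadjusted comparison could present ordinary hospital-to-hospital variation as an intervention effect.

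**Working it through.** **Inputs from Sample size and Allocation.** 180 patients per arm; 12 hospitals, six per arm; 30 per hospital; ICC 0.082; proportions 0.50 and 0.22; one-sided alpha 0.05; stated power 93%. Strata: eight hospitals split 4:4 and four split 2:2.

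**1. Reproduce the stated power.**
- Design effect = 1 + (30 − 1) × 0.082 = 3.378.
- Effective n per arm = 180 / 3.378 = 53.3.
- Unpooled standard error = √[(0.50 × 0.50 + 0.22 × 0.78) / 53.3] = 0.089.
- Power = Φ(0.28 / 0.089 − 1.645) = 93.4%; the pooled-variance version gives 92.3%.

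The stated 93% is reproduced with the clustering included, so the trial's own sizing depends on it.

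**2. Size of a test that ignores clustering.** The naive standard error is too small by √3.378 = 1.84.
- Two-sided 5%: 2 × [1 − Φ(1.96 / 1.84)] = 28.6%.
- One-sided 5%: 1 − Φ(1.645 / 1.84) = 18.5%.

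**3. Sensitivity.** The article gives no ICC for either time outcome, so the ICC is varied as an assumption (30 per hospital unless stated):

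| ICC | Design effect | Two-sided size | One-sided size |
|---|---|---|---|
| 0.02 | 1.58 | 11.9% | 9.5% |
| 0.05 | 2.45 | 21.1% | 14.7% |
| 0.082 | 3.378 | 28.6% | 18.5% |
| 0.082, 40 per hospital | 4.198 | 33.9% | 21.1% |

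The last row is included because Sample size expects some hospitals to pass 30. In the other direction, if the strata removed half the between-hospital variance (an assumption), the design effect would be 1 + 29 × 0.041 = 2.19 and the two-sided size about 18.5%.

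**4. Check on the log-rank test itself.** In 4,000 simulated trials per setting (12 hospitals of 30, lognormal hospital frailty, no arm effect, follow-up to day 30), the unadjusted two-sided log-rank test rejected in 29.7% at a day-30 ICC of about 0.084 and in 12.3% at about 0.02. The one-sided rate at 0.084 was 18.2%. The design-effect formula is therefore a fair guide for a 30-day window.

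**5. A clustered alternative.** The stratified randomisation allows C(8,4) × C(4,2) = 70 × 6 = 420 allocations. In 2,000 simulated trials per setting at ICC 0.082, a log-rank statistic referred to those allocations rejected a true null in 4.4% to 5.5%.

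**The case against.** The strongest reply is that no faulty test is planned. The article specifies no log-rank test, p-value, confidence interval or band for either time comparison, and it calls the time-to-success curves a display. A reader might infer that the plan commits to overstated precision; the text does not support that, and this part of the objection stands in full. The 28.6% therefore describes what would happen under one natural choice of test.

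A second reply is that a journal article condenses, and the full protocol or analysis plan may name a clustered method. That is possible. But this article states how clustering is handled for almost every other comparison, including baseline tables, so the exception is more than ordinary brevity. If the curves are only descriptive, the promised between-arm comparison has no stated method; if they are inferential, the only named method omits the hospitals.

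A third reply is that mortality needed its own clustered model because the carry-over sentence does not mention it, so the frailty sentence need not imply unadjusted tests elsewhere. That is a fair reading: each of the four main outcomes does have a clustered method. It still leaves the two time comparisons without one.

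Finally, these analyses are supplementary. The Discussion says that only the 30-day primary outcome is adequately powered, and the hospitals were selected for homogeneity. That limits the weight of the point without removing it.

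**Conclusion.** The point holds as a gap in the named method: two pre-specified between-arm time comparisons have no stated analysis that accounts for hospital randomisation, although time to death does. The primary analysis, and the clustered analyses of ART initiation within 90 days, viral suppression and mortality, are not affected.

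The size is conditional. About 28.6% applies to a standard two-sided 5% log-rank test, 30 patients per hospital and ICC 0.082. That ICC was given for the binary primary outcome. The only test level the article states, one-sided 5%, gives about 18.5%.

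Two stronger readings should be avoided. First, 28.6% is not a floor: a lower ICC, a one-sided test or effective stratification reduces it, though every case computed stays above 5%. Second, a reader might infer still larger errors for long follow-up. Simulation with exponential times does give 41.8% at 90 days and 48.9% at 365 days, but the article supports no such time distribution. A constant rate of 0.22 per 30 days would imply 1 − 0.78⁶ = 77% success by 180 days. The Background figures of 43% receiving confirmatory testing and 57% of confirmed cases receiving CD4 testing within 6 months multiply to about 25%, if they may be combined at all.

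**What to change.** In Data analysis, name a clustered between-arm method for time to testing success and time to ART initiation. Either of these would do:

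- the shared-frailty Cox model already planned for death, fitted to both times with hospital as the cluster and covariates as planned; or
- a log-rank statistic referred to the 420 allocations possible within the two randomisation strata. This follows the randomisation directly and is close to the permutation over hospitals already used for baseline variables. Its smallest two-sided p-value is 2 / 420 = 0.005. The size of the frailty model with only 12 hospitals was not checked here, which favours the permutation for the p-value.

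State that the Kaplan-Meier curves are descriptive, and attach to them no p-value or interval that ignores clustering.

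The cost is two extra model fits (or a short permutation routine) on data already collected. No patients are added. The downside is wider intervals and less striking p-values for these two comparisons.
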